### **C. Sample size, statistical methods, and power calculation**

**Outcomes. The primary outcome of SA 1** will be receipt of appropriate treatment (onsite or referral, as indicated) for clients with a positive screen. Figure 5 illustrates treatment scenarios for women with a positive screen and the targeted timeframe for treatment. Women with coinfections (cervicitis/STI) must receive treatment, resolution, and rescreening within 3 months to determine infection status and appropriate action. Patients with a positive screen for precancerous lesions should ideally receive same day onsite treatment with cryotherapy (max duration of 5 days/1 wk) or referral (in/outside facility) to LEEP for advanced lesions (w/in 5 days/1 wk) with treatment follow-up and negative rescreen. If suspected of invasive CC, a referral to KNH or MTRH for chemo/ radiotherapy within the month.

We will identify women presenting with precancerous lesions (mild, moderate or severe), suspicious of invasive CC, or those with unreliable screen results due to cervicitis/STI or other comorbidity in each arm. We will then determine if guideline adherent treatment was provided based on severity of screening results. Retention time from first screening to last follow-up will also be calculated and compared by arm. Patient and facility-level factors, including aggregated provider characteristics, will be assessed for their moderating impact on receipt of appropriate treatment after a positive screen. To assess pathways through which the CATSystem works, we will measure provider and patient information, knowledge and motivation as potential mediators pre- and post-intervention across arms.

Secondary Outcome: We will determine whether each participant is screened for CC during the intervention period and use these data to assess the effect of the CATSystem intervention on odds of screening. To adjust for sites' pre-intervention screening rates, we will compute the proportion of women screened for CC cancer during the pre-intervention period and include this variable as a covariate in modeling.

**Statistical analyses for SA1 primary outcome.** To demonstrate the efficacy of CATSystem verses SOC to increase the odds of women with a positive screen receiving treatment, we will model odds of treatment as a function of study arm and selected covariates (e.g., age, partner support, HIV status) using a logistic mixed model with a random site intercept included to adjust for clustering. Between-within degrees of freedom specified to adjust for downward bias in standard error estimates when the number of clusters is not large. Matching of sites prior to randomization will improve balance between arms on site-level

characteristics. Inclusion of covariates in the model will provide additional control for between-arm differences. We will use propensity score weighting to adjust for any severe, unanticipated imbalance between arms.

In post hoc analyses we will explore baseline patient and facility-level characteristics as potential correlates and moderators of the effect of CATSystem. Effects of these characteristics will be assessed by adding main effect and study arm×characteristic interaction terms to the logistic mixed model described above. We will also examine changes from baseline for key individual level factors [HIV status, partner support (see patient baseline survey in appendix)] for the two study arms. In further analyses, we will examine provider [level of experience, knowledge and motivation (see Provider survey in appendix)] as a mediator of the intervention's effect on odds of receiving treatment by fitting two models for each domain score: (1) A generalized or linear mixed model with change in knowledge from baseline to end of study as outcome and study arm as explanatory variable, and (2) a log-binomial mixed model with receipt of treatment as (binary) outcome and change in provider knowledge from baseline to end of study as explanatory variable. Estimates from these models will be combined to assess direct and indirect effects of the intervention. We will similarly assess provider motivation, participant knowledge, and participant motivation as potential mediators.

**Sample size considerations.** Assuming average success (treatment completion) rates of 0.10 (SOC arm) and 0.35 (CATS arm), we used R to simulate 5,000 data sets, each with outcome data for five 30-person clusters per arm. A target ICC value for each data set was randomly drawn from a half-normal distribution fit by Turner et al. (2001) to the empirical distribution of 70 ICCs from studies of health outcomes with data clustered within practices, towns, or postal codes. For simulation, each target ICC was converted to a random site intercept variance on the logistic scale using the assumed SOC success rate (0.10) and the Taylor expansion approximation from Turner et al. We simulated success counts for each cluster by drawing a random cluster intercept from a Gaussian distribution with the specified variance, adding the appropriate fixed intercept and (for CATS sites) arm effect on the logistic scale, converting the resulting logit to a probability (p), and taking a random Binomial(30, p) draw. This process reflects our uncertainty in the true ICC. It also produces ICCs larger than the target values because of bias in the Taylor approximation and our use of the SOC success rate to estimate the random intercept variance, which yields a larger ICC among CATS clusters due to their higher success rate. Thus, across the 5,000 data sets, mean ICC was 0.057 for SOC clusters and 0.083 for CATS clusters (vs. mean ICC 0.023 for the half-normal distribution fit by Turner et al.). For a point of comparison, analysis of pilot screening rate data for our ten study sites yielded ICC 0.012.

For each simulated data set we used SAS 9.4 to fit a logistic mixed model with a fixed arm effect and random site intercept. Between-within degrees of freedom were specified as a small-sample adjustment. The mean length of 95% CIs for the arm effect odds ratio was 18.0; power (1-sided test,  $\alpha=0.025$ ) was 86.9%. For comparison, the R package *clusterPower* (<https://CRAN.R-project.org/package=clusterPower>), which has been verified against NIH's GRT Sample Size Calculator and PASS11, yielded power=85.9% for the SOC and CATS rates and ICC=0.05.

The proportion of screened women with a positive result ranged between 3.4% (53/1576) during the SOC period and 7.1% (39/550) during the intervention period. **To guide enrollment targets, we will assume a positive screen rate of 5%, which would require enrollment of at least n=600 women per cluster to result in 30 women with a positive screen. We will enroll an additional 10% to account for attrition due to relocation, transfer of health facility or death.** During our pilot study, we enrolled 552 patients at the pilot facility over the span of 15 months, however, several months were impacted by Covid-19 restrictions at the health facility (n=3) or a clinical worker strike (n=1) when enrollment numbers dropped from an average of 53 to 24 patients per month. We thus estimate the potential to have enrolled up to 795 patients under more normal conditions. We also anticipate that monthly enrollment numbers may decrease over the 24-month period, given that once a woman has been screened and/or treated, their next screening appointment per guidelines would be within 3 to 5 years; thus fewer women at the health facility will be eligible for screening over the course of the study. With this in mind, **we expect a 24 month enrollment**

**period will be adequate to reach a total of 660 participants at each hospital (660 x 10 sites= 6,600 study participants).**

**Missing data; multiple testing.** Taking an intent-to-treat approach, rather than exclude participants who drop out from analyses we will carry out and compare two analyses, one where dropouts are classified as not receiving treatment, and another where inverse probability of attrition weighting is used to adjust for participants lost to attrition. Missing data on explanatory variables will be imputed using stochastic regression imputation or, if the rate of missing data exceeds 1%, using multiple imputation by chained equations. Consistent with guidance from the statistics community, we will focus on effect sizes and their confidence intervals rather than treating  $p < 0.05$  as a dichotomous indicator of whether an effect is practically important and classifying results as “significant” or “not significant” on this basis. Model selection processes that exploit chance will be avoided.

**Analysis plan for secondary outcome of CC screening.** As for the primary outcome, we will assess the CATSystem effect for the secondary outcome by modeling odds of CC screening as a function of study arm using a logistic mixed model with a random site intercept, specifying between-within degrees of freedom. In addition, we will adjust for sites’ pre-intervention screening rate by including this variable as a covariate. This is similar to computing a change score for each site and assessing the between-arm “difference in differences” but (1) allows modeling data at the patient level and examination of patient-level characteristics as correlates of outcomes, and (2) involves estimation of a regression coefficient reflecting association between sites’ pre- and post-implementation screening rates, thereby avoiding assumption of perfect reliability implicit in the change score approach. We used the R package *clusterPower* to estimate statistical power for this outcome, assuming an SOC screening rate of 15% (an improvement from the 10.5% rate observed in our pilot data), a CATSystem screening rate of 30%, and an ICC of 0.04, four times the ICC observed for the ten study sites’ screening rates in our pilot data. The proposed sample size (600 study completers per site) yields 82.5% power for a 1-sided tests at  $\alpha = 0.05$ . This does not account for reduction in error variance we will gain by including sites’ pre-intervention screening rates as a covariate in modeling.

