## **B. Study Type and Design:**

We propose a cluster randomized controlled trial (SA1) enrolling CC screening clients at Kenyan health facilities: n=5 intervention and n=5 matched standard of care (SOC) sites to evaluate the efficacy of the CATSystem to improve guideline-adherent CC screening, treatment, referral and follow-up. SA2 will focus on the feasibility and acceptability of CATSystem implementation, and SA3 assesses the cost-effectiveness of the CATSystem and considerations for scale-up.

**Study Setting:** Kenya has a population of over 50 million people, of whom approximately 59.4% are reproductive age girls/women (15-64yrs). Proposed study sites will be in the Western Kenyan counties of Siaya and Busia where HIV prevalence is among the highest nationally, contributing to increased risk for cervical cancer. Siaya has a population of 993,183 (53% female) and the highest prevalence of HIV in Kenya (21%). Busia has an estimated population of 908,658, (52% female) and the 5th highest HIV prevalence in Kenya at 7.7%. The overall adult literacy rate is 81.5% in Kenya and 75.3% in Siaya and Busia. We have ensured our text messages have a 3 to 5 Flesch-Kincaid grade level. Table 1 details facility level data from the 10 most closely matched study sites from a recent retrospective review of 19 potential hospitals. Priority data points include the number of women: of reproductive age, living with HIV, screened for CC in the past year. We carefully reviewed and described the procedures and capacity for CC screening and treatment at each planned study site to ensure similarity across to optimize matching prior to randomization.

Table 1. Proposed matches from data reviewed October 2021 to September 2022

| Site                          | Busia | Bondo | Port Victoria | Akala | Matayos | Ukwala | Yala | Alupe | Nambale | Khunyangu |
|-------------------------------|-------|-------|---------------|-------|---------|--------|------|-------|---------|-----------|
| Repro aged women in care      | 51551 | 21368 | 8500          | 7060  | 5450    | 7196   | 6236 | 6000  | 5065    | 4156      |
| Women in HIV care (CCC)       | 3306  | 1200  | 591           | 2018  | 370     | 663    | 1271 | 249   | 700     | 1137      |
| Total screen/rescreen         | 4440  | 1878  | 1087          | 1003  | 359     | 477    | 617  | 478   | 730     | 615       |

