#### **D. Subject Criteria (See Vulnerable Populations appendix, if applicable):**

**Health Facility Eligibility and Selection.** Eligible sites must provide CCC and MCH/FP services and serve an average at least 4000 reproductive aged women. A repeated assessment of the previous three months will be conducted prior to study start to capture any changes that may require adjustments to the planned sites. All eligible facilities will be yoked in pairs matched on volume of reproductive aged women, average number of women screened per month, and screen and treat capacity. The study statistician will randomly allocate one site in each pair to the intervention.

**Participant Eligibility and Consent.** Eligibility will be restricted to women >16 years of age (age of treatment consent is 16 yrs) with access to a cell phone and ability to read SMS’s at a 3rd-5th grade level. While literacy levels in Bungoma and Busia are high, women can opt to customize SMS messages to include pre-specified familiar greetings or numbers to indicate the need to contact or return to the health facility (e.g. ‘afya’ [Swahili for healthy] or ‘7777’). To maximize generalizability, all women receiving CC screening at CCC or MCH/FP during the study period will be eligible for enrollment. Pregnant women (>20 weeks) who are not eligible for CC screening per Kenyan guidelines, incarcerated patients or women with impaired mental capacity affecting ability for informed consent will be excluded from the study. Women opting out of the study will be offered standard CC screening services without CATSystem enrollment. All participants will be informed of the purpose of the research, including potential benefits and risks, prior to a request for written informed consent. Guardians of eligible girls <18 years of age will be required to sign a written, informed consent and the eligible girl will be asked to provide written assent. Site Research Assistants (trained lay health workers) familiar with CC screening procedures and providers will document study enrollment and enrollment refusal at all sites.

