**III. Subject Participation**

**A. Recruitment:** All women who receive cervical cancer screening at study hospitals will be offered enrollment into the study. Clinical staff or the research assistant may identify eligible women from the Maternal and Child Health/Family Planning (MCH/FP) or comprehensive care centers (CCC). Once identified, the research assistant assigned to each site will inform eligible women about the purpose of the study, will describe risk/benefits of the study, and will describe what to expect from participation in the study before asking women if they'd like to enroll in the study. At control sites, the standard of care services will be described to participants. At intervention sites, the standard of care services and the unique communication features of the CATSystem will be described to patients. Eligible women will sign a written informed consent form in either Kiswahili or English (per the participant's preference) prior to enrollment. If a woman is non-literate, a thumbprint will be used in lieu of a written signature. Upon enrollment, the RA will conduct a brief enrollment survey with each participant. Participant will be remunerated \$2.00 for participating in the enrollment survey, in appreciation of their time.

**B. Screening Interview/questionnaire:** N/A

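### The secondary screening outcome is defined among women enrolled because they are being screened, so it sits near ceiling and the 82.5% power does not describe that population

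*Protocol*

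**What the plan says.** **Outcome.** Protocol section II.C, repeated in V.B, sets the secondary outcome at the level of the participant: "We will determine whether each participant is screened for CC during the intervention period". The analysis paragraph in II.C fits a patient-level logistic mixed model with a random site intercept and takes each site's pre-intervention screening rate as a covariate.

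**Who becomes a participant.** Section II.B describes the trial as "enrolling CC screening clients at Kenyan health facilities". Section II.D says "all women receiving CC screening at CCC or MCH/FP during the study period will be eligible for enrollment". Section III.A says "All women who receive cervical cancer screening at study hospitals will be offered enrollment into the study".

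**Enrolment target.** Section II.C assumes 5% positivity, "which would require enrollment of at least n=600 women per cluster to result in 30 women with a positive screen".

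**Power for the secondary outcome.** The same section computes power "assuming an SOC screening rate of 15% (an improvement from the 10.5% rate observed in our pilot data), a CATSystem screening rate of 30" per cent, and concludes: "The proposed sample size (600 study completers per site) yields 82.5% power for a 1-sided tests at" 0.05.

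**The concern.** A woman enters the study by being screened, and the outcome then asks whether she was screened. No section describes enrolling unscreened women, or counting them as a denominator during the intervention period. Among participants the outcome has almost no room to vary, so there is almost nothing for an arm effect to act on.

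The two calculations in II.C also make incompatible assumptions about the same 600 women per site. The enrolment target needs all of them screened. The secondary power calculation needs 15% or 30% of them screened.

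At stake is the second of the two Aim 1 hypotheses, that the CATSystem raises screening rates. Followed literally, the planned model would return an inestimable or uninformative odds ratio. The team would then have to choose a denominator after seeing data.

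**Working it through.** **Inputs.** From II.C: 15% against 30%, 600 per site, one-sided alpha 0.05, and "an ICC of 0.04, four times the ICC observed for the ten study" sites. From II.B: 5 sites per arm, and Table 1.

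**1. Reproduce the stated power.** Unpooled comparison of two proportions with a design effect and a noncentral t distribution on 2 × (5 − 1) = 8 df.
- Design effect: 1 + (600 − 1) × 0.04 = 24.96.
- Effective n per arm: 3,000 / 24.96 = 120.2.
- Noncentrality: 0.15 / √[(0.15 × 0.85 + 0.30 × 0.70) / 120.2] = 0.15 / √(0.3375 / 120.2) = 2.831.
- Power: 82.5%, as stated.

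The same formula gives 85.9% for the primary outcome (10% against 35%, 30 per site, ICC 0.05, one-sided 0.025), which is the protocol's comparison figure. The arithmetic is sound. The question is which population the inputs describe.

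**2. Put the two uses of 600 side by side.**

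| Assumption | Screened per site | Positives per site at 5% |
|---|---|---|
| Enrolment target (all screened) | 600 | 30 |
| Secondary power, SOC (15%) | 90 | 4.5 |
| Secondary power, CATSystem (30%) | 180 | 9 |

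Only the first row agrees with the recruitment text and with the 30 positives that the primary outcome needs.

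**3. What the literal outcome can show.** At 100% against 100%, the difference and the binomial variance are both zero, so the odds ratio is not estimable. If a few enrolled women go unscreened, the rates fall a little below 100%. For assumed near-ceiling rates (not in the protocol), with the other inputs as in step 1:
- 98% against 99%: power 14%.
- 99% against 99.9%: power 22%.
- 95% against 99%: power 51%.

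**4. Where 15% and 30% appear to come from.** II.C presents 15% as an improvement on a 10.5% pilot rate. Table 1 divides screens by reproductive-age women in care. Its ten site percentages (8.6, 8.8, 12.8, 14.2, 6.6, 6.6, 9.9, 8.0, 14.4, 14.8) sum to 104.7, a mean of 10.47%. Pooled, the table gives 11,684 / 122,582 = 9.5%. The match of 10.47% with 10.5% suggests that the rate is per woman in care, not per enrolled participant.

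**5. Power on that denominator.** Same rates, ICC and alpha, with equal site sizes assumed.

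| Women per site | Source in Table 1 | Design effect | Effective n per arm | Power |
|---|---|---|---|---|
| 4,156 | smallest site | 167.2 | 124.3 | 83.6% |
| 6,648 | median | 266.9 | 124.6 | 83.7% |
| 12,258 | mean (122,582 / 10) | 491.3 | 124.8 | 83.7% |

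Power barely moves because the effective n per arm cannot exceed 5 / 0.04 = 125, however large the sites are.

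**The case against.** The best defence is that a facility screening rate was meant all along. Hypothesis 2 speaks of rates adjusted for pre-implementation rates, the covariate is a site proportion, and the 10.5% matches Table 1. On that reading the stated power is slightly conservative. This stands as evidence of intent, and it rules out reading the protocol as making Hypothesis 2 untestable in principle. It does not rescue the text: II.C and V.B define the outcome per participant, the analysis paragraph gives patient-level modelling as a reason for its approach, and power is computed on 600 completers.

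Second, enrolment may precede screening. The care steps in I.C list enrolment before screening, and the enrolment survey asks about motivation to be screened. Some consenting women may therefore go unscreened. That stands too, and is why the outcome is better called near ceiling than constant. It gives no support to 15% or 30%.

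Third, rescreening might have been intended. The outcome is not defined that way, and II.C puts the next routine screen 3 to 5 years away, beyond the 24-month enrolment period.

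A reader might also infer that the primary outcome is short of positive screens, from the 4.5 and 9 in the working. That would follow only if recruitment were changed so that 15% or 30% of participants were screened. Nothing in the protocol proposes this.

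**Conclusion.** The point holds as an internal contradiction over population and denominator. As written, the secondary outcome is near ceiling in both arms, the patient-level model cannot test Hypothesis 2, and neither the 600 completers per site nor the 82.5% describes the enrolled women. This is not a detail left to an SAP, because the protocol itself fixes the population, the unit of analysis and the power.

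The conclusion rests on two inferences. One is that nearly all participants are screened, which follows from the eligibility, recruitment and enrolment-target text. The other is that 15% and 30% refer to women in care, which follows from the match with Table 1.

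The numerical consequence is small once the denominator is corrected: about 83.6% to 83.7% against 82.5%, provided that ICC 0.04 and one-sided 0.05 are kept. The primary outcome, its recruitment and its power are untouched.

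**What to change.** In II.C (outcome and analysis paragraphs) and V.B, define the secondary outcome per site:
- **Numerator:** women screened at the site during a fixed intervention period. Count each woman once, or report screens and rescreens separately, because Table 1 combines the two.
- **Denominator:** reproductive-age women in care at that site in the same period.
- **Model:** binomial mixed model with arm, a random site intercept, between-within degrees of freedom, and the pre-intervention rate over a period of the same length as covariate.
- **Power:** replace the 600-completer statement with about 83.6% to 83.7% for 15% against 30%, ICC 0.04, one-sided 0.05, assuming 4,156 to 12,258 women per site. State that equal site sizes are assumed; Table 1 sites range from 4,156 to 51,551.

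Make the change before arm-level screening data are seen.

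**Cost.** No extra participants, but some extra data. As described in II.B, the facility assessment form covers annual screening volume but not reproductive-age women in care. That count must be added at start, mid-point and end, and repeat screens must be separable in the registers. Patient-level covariate modelling for this outcome is lost, so the sentence in II.C that claims it as an advantage should go.

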**Provider surveys:** At baseline and at the end of the study, providers in both arms will be asked to complete a survey (See Appendix 5). The survey will assess provider role/department, level of experience, knowledge and motivation regarding current CC screen and treat guidelines, and barriers and facilitators to provision of complete CC screening services. End of study surveys will also include level of direct engagement with CATSystem and adapted quantitative items from the Acceptability of Intervention Measure (AIM), Intervention Appropriateness Measure (IAM), and Feasibility of Intervention Measure (FIM) four-item measures of implementation outcomes that are often considered “leading indicators” of implementation success. Providers will be eligible to complete the survey if they (1) work primarily in CCC, laboratory, or MCH/FP departments, (2) will/have been involved in the provision of CC screening and treatment during the course of the study, and (3) have interacted with the CATSystem during the course of the study (intervention sites only). We estimate n=5 providers per site for a total of n=50 provider surveys (n=25 intervention, n=25 control). Providers will complete informed consent prior to surveys.

**Supportive Supervision Visits** will occur monthly at all sites. Site Coordinators will provide technical assistance and retraining, review study materials (informed consent forms, surveys), and review data for completeness and accuracy. The monthly frequency of site visits has been adequate in previous HITSystem studies.

Aim 2 methods will include surveys and focus groups with CATSystem users, described below:

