**V. Data Analysis and Reporting**

**A. Statistical and Data Analysis:** To demonstrate the efficacy of CATSystem verses SOC to increase the odds of women with a positive screen receiving treatment, we will model odds of treatment as a function of study arm and selected covariates (e.g., age, partner support, HIV status) using a logistic mixed model with a random site intercept included to adjust for clustering. Between-within degrees of freedom specified to adjust for downward bias in standard error estimates when the number of clusters is not large. Matching of sites prior to randomization will improve balance between arms on site-level characteristics. Inclusion of covariates in the model will provide additional control for between-arm differences. We will use propensity score weighting to adjust for any severe, unanticipated imbalance between arms.

In post hoc analyses we will explore baseline patient and facility-level characteristics as potential correlates and moderators of the effect of CATSystem. Effects of these characteristics will be assessed by adding main effect and study arm×characteristic interaction terms to the logistic mixed model described above. We will also examine changes from baseline for key individual level factors [HIV status, partner support (see patient baseline survey in appendix)] for the two study arms. In further analyses, we will examine provider [level of experience, knowledge and motivation (see Provider survey in appendix)] as a mediator of the intervention’s effect on odds of receiving treatment by fitting two models for each domain score: (1) A generalized or linear mixed model with change in

knowledge from baseline to end of study as outcome and study arm as explanatory variable, and (2) a log-binomial mixed model with receipt of treatment as (binary) outcome and change in provider knowledge from baseline to end of study as explanatory variable. Estimates from these models will be combined to assess direct and indirect effects of the intervention. We will similarly assess provider motivation, participant knowledge, and participant motivation as potential mediators.

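### The exploratory mediator models use raw change scores and leave out the baseline score that is collected, which distorts the mediator–treatment slope and usually costs precision for the arm effect

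*Protocol*

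**What the plan says.** Protocol II.C (statistical analyses for the SA1 primary outcome) sets out two models per domain score. Model (1) is "A generalized or linear mixed model with change in knowledge from baseline to end of study as outcome and study arm as explanatory variable". Model (2) is a "log-binomial mixed model with receipt of treatment as (binary) outcome and change in provider knowledge from baseline to end of study as explanatory variable". Each names one explanatory variable and no baseline score. The two are then joined: "Estimates from these models will be combined to assess direct and indirect effects of the intervention". The approach is extended to three more mediators: "We will similarly assess provider motivation, participant knowledge, and participant motivation as potential mediators". Section V.A repeats both models.

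The baseline scores exist. Under Provider surveys (II.B): "At baseline and at the end of the study, providers in both arms will be asked to complete a survey". Under Participant surveys, the enrollment survey in both arms covers knowledge and motivation, and women who screen positive are later asked the same measures again.

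For the secondary outcome, screening, II.C does something different. It enters each site's pre-intervention rate as a covariate, "thereby avoiding assumption of perfect reliability implicit in the change score approach", and expects lower error variance as a result. The protocol gives no reason for handling the survey scores differently.

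**The concern.** Survey scores of knowledge and motivation are measured with error, so a provider or woman who starts low tends to show a larger change through regression to the mean alone. Change is therefore negatively correlated with baseline.

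In model (2), where baseline is omitted, the coefficient on change mixes the effect of the end score with the opposite of the baseline effect. This is bias, and a larger sample does not remove it. Because the two models are combined, it passes into the indirect effect, so a real knowledge pathway could be reported as weak or absent.

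In model (1) randomisation protects the arm effect from bias. What is lost there is precision, with only about 25 providers per arm at five sites.

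**Working it through.** **Inputs from the protocol:** 5 sites per arm; an estimated 5 providers per site; at least 30 women with a positive screen per site.

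**Assumed, because the protocol gives none for the mediators:** baseline–end correlation ρ = 0.5 (range 0.3–0.7); ICC 0.05; effects of 0.8 SD (providers) and 0.4 SD (women); unit SD at both times; two-sided 0.05; t with 8 df.

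**Check of the method.** The protocol states no power for these models, so the approach (design effect, noncentral t, 8 df) was tried on its neighbouring figures.
- Primary: SE = √[(0.09 + 0.2275) × (1 + 29 × 0.05)/150] = 0.0720; 0.25/0.0720 = 3.47; power 85.9% at one-sided 0.025, as stated.
- Screening: SE = √[(0.1275 + 0.21) × (1 + 599 × 0.04)/3000] = 0.0530; 0.15/0.0530 = 2.83; power 82.5% at one-sided 0.05, as stated.

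**Model (2).** Let log-risk = a + b0 × baseline + b1 × end score. With equal variances and no arm shift, the slope on change alone is

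(b1 − b0)(1 − ρ) / [2(1 − ρ)] = (b1 − b0)/2, for any ρ.

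If the end score shifts by D SD between equal-sized arms and arm is not in the model, the slope is

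[(b1 − b0)(1 − ρ) + b1 D²/4] / [2(1 − ρ) + D²/4].

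At ρ = 0.5:

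| b0 | b1 | Change only, D = 0 | Change only, D = 1 | Change slope with baseline added |
|---|---|---|---|---|
| 0 | 0.30 | 0.15 | (0.15 + 0.075)/1.25 = 0.18 | 0.30 |
| 0.15 | 0.15 | 0.00 | 0.0375/1.25 = 0.03 | 0.15 |
| 0.30 | 0.15 | −0.075 | (−0.075 + 0.0375)/1.25 = −0.03 | 0.15 |

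Simulation (400,000 independent units, log link) agreed to within 0.005. Adding study arm without baseline does not repair the slope: within arm it is again (b1 − b0)/2.

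The size depends on equal variances. With end-to-baseline SD ratio k the D = 0 slope is [b1(k² − ρk) − b0(1 − ρk)] / (1 + k² − 2ρk). For b0 = 0, b1 = 0.30, ρ = 0.5 this gives 0.086 at k = 0.8 and 0.203 at k = 1.2.

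Indirect effect, as the product on the log scale: with a 0.8 SD arm effect, b0 = 0, b1 = 0.30 and ρ = 0.5, the change-only slope is (0.15 + 0.048)/1.16 = 0.17. The product is 0.8 × 0.17 = 0.14, against 0.8 × 0.30 = 0.24.

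**Model (1).** Let s be the correlation of a site's effect between baseline and end, and m the number per site. The variance of a site mean is
- change: 2(1 − s) × ICC + 2(1 − ρ)(1 − ICC)/m
- adjusted for individual baseline: ICC × (1 + ρ² − 2ρs) + (1 − ρ²)(1 − ICC)/m

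and the SE of the arm difference is √(2 × variance/5). With s = ρ the variance ratio, adjusted over change, reduces to (1 + ρ)/2, or 0.75 at ρ = 0.5.

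At ρ = 0.5:

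| Group | s | Variance, change / adjusted | Power, change / adjusted |
|---|---|---|---|
| Providers, m = 5, 0.8 SD | 0.5 | 0.240 / 0.180 | 62% / 74% |
| | 0.8 | 0.210 / 0.165 | 68% / 78% |
| | 1.0 | 0.190 / 0.155 | 72% / 80% |
| Women, m = 30, 0.4 SD | 0.5 | 0.0817 / 0.0613 | 50% / 61% |
| | 0.8 | 0.0517 / 0.0463 | 68% / 73% |
| | 0.9 | 0.0417 / 0.0413 | 77% / 78% |
| | 1.0 | 0.0317 / 0.0363 | 87% / 83% |

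With s = ρ, the provider gain is 18 points at ρ = 0.3 and 5 points at ρ = 0.7.

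**The case against.** **These are exploratory analyses whose covariates a statistical analysis plan could settle.** It is true that they are exploratory: no power, alpha or decision rule is attached, and model (2) as worded does not even name study arm, so the list of terms may be incomplete. But the protocol does more than stay silent. It writes out both models, in two places, with change as the variable and one explanatory variable each, whereas its primary model allows for selected covariates. A stated form can be improved.

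**A reader might infer that the protocol contradicts itself or rejects change scores in general.** It does not. The screening paragraph calls its own method similar to a change-score comparison and states a preference for one outcome. This is an inconsistency of approach.

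**A reader might infer that baseline adjustment always gains power.** Change scores cancel stable site effects, and with 30 women per site that matters: the gain is nearly gone at s = 0.9 and becomes a loss at s = 1.0. For providers the gain shrinks but persists at ICC 0.05. With a higher mediator ICC (0.2 or more) and fully stable site effects, change can match or beat individual-baseline adjustment for providers too.

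**A reader might expect a reversed sign in model (2).** With equal variances and no arm shift, that needs baseline to matter more than the end score, and nothing in the protocol suggests it does. Attenuation is the better-supported concern.

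**For providers, model (2) may rest on ten site values.** The outcomes paragraph speaks of aggregated provider characteristics. If scores are aggregated, a baseline term costs a between-site degree of freedom and the slope will be imprecise either way. That cost is real, but it does not remove the bias.

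**Conclusion.** The point holds for the exploratory mediator models, as a free improvement. Model (2) carries the main harm. Under equal variances its slope is about (b1 − b0)/2: roughly half the truth if only the end score matters, and near zero if both scores matter equally. An arm shift softens this slightly. In model (1) the arm effect is unbiased and only precision is at stake: about 8 to 12 points of power for providers at ρ = 0.5, and for women from about 12 points down to none or a small loss.

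The correlation, effect sizes, mediator ICC, site stability and equal variances are all assumptions. The direction of the model (2) problem is firmer than its size.

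A reader might extend the point to the efficacy conclusions or to the partner-support comparison. Neither extension is supported: the primary and secondary analyses do not use these models, and for partner support the protocol says only that changes will be examined, without fixing a model.

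**What to change.** In II.C and V.A:
- Model (1): add the individual baseline score as a covariate. The outcome may be the end score or the change; the arm estimate is the same.
- Model (2): add the baseline score beside the change (or end) score, at the same level of aggregation.
- Apply this to provider knowledge, provider motivation, participant knowledge and participant motivation.
- Handle missing baseline scores by the rule the protocol already has for explanatory variables (stochastic regression imputation, or multiple imputation by chained equations above 1% missing), not by filling in a site mean.

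The cost is a change of wording and one already collected covariate per model, with a degree of freedom where provider scores are aggregated to site. No data collection or site procedure changes. It should be settled before results are seen.
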